
### Analysis of mechanistic outcomes

The mechanistic outcomes from all the physiological balance tests will be the EMG characteristics (burst slope, burst area and onset timing [11,17,48]) and displacement of the whole body COM with respect to the centre of pressure (CP) including postural sway. The calculation of the COM using the motion capture software provides a measure of whole body movement. During feet-in-place tasks, CP displacement is representative of the body’s active control of balance which aims to maintain the COM safely within the base of support provided by the feet [49]. EMG onset timing, burst slope and area reflect the speed and magnitude of activation of postural muscles in anticipation of, or in response to balance perturbations.*Centre of mass-centre of pressure (COM-CP) displacement*: The resultant ground reaction force data will be used to calculate the CP. The antero-posterior and medio-lateral coordinates of the COM position and the CP will be calculated for each data sample and used to calculate the resultant distance between the COM and CP in the transverse plane (COM-CP displacement). We will identify the maximum COM-CP displacement during each trial for physiological balance activities 2 *b-e.* These parameters will also be used to quantify postural sway in quiet stance (activity *2a).**Timing of EMG onset:* The onset of muscle activation burst (in milliseconds) will be calculated relative to the onset of the arm acceleration in the internal perturbations, the onset of load release for external perturbations, and onset of knee movement of the stepping leg for stepping reactions [15] for each trial.*EMG burst slope and area:* The EMG burst area will be calculated separately for each trial. The EMG burst slope will be calculated from the average of the repeated trials. These parameters will reflect the timing and magnitude of the burst above quiet stance state and will be normalized to maximum EMG recorded on the Biodex.

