## Background

Balance ability is one of the most important factors in determining independence in daily activities and risk of falls following stroke [1]. Dynamic balance and mobility or ‘walking balance’ can be described as the ability to control the centre of mass (COM) within the base of support to remain upright during ambulation [2] and encompasses a range of walking-related tasks which challenge the balance system. The impact of diminished dynamic balance can be significant for stroke survivors. The resulting mobility limitations are associated with decreased self-efficacy, loss of independence, and restrictions in activities of daily living, community integration, and quality of life [3,4].

People following stroke struggle to produce sufficient power (the product of force and speed) with their paretic muscles; deficits in speed of movement are well-documented after stroke [5,6]. It has been suggested that power may be more important than absolute force production in functional mobility tasks, and velocity of movement may be instrumental to counteract potentially destabilizing forces exerted on an individual’s COM by gravity and environmental interactions (external perturbations) as well as voluntary movements (internal perturbations) [7,8]. Modest perturbations to quiet stance can be accommodated using an inverted pendulum model of balance control [9] in which the ankle musculature plays a pivotal role in the maintenance of stance, while activation of muscles around the hips is essential in responding to larger perturbations [10,11], particularly if a step is required to maintain balance - termed a stepping reaction [12]. There may be a greater reliance on stepping behaviours to avoid a fall after stroke than in healthy individuals [13]; however, impairments in paretic muscle activation make it difficult for these individuals to step with sufficient speed, coordination and amplitude to effectively to regain their balance [7,14,15].

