### Data collection methods

Kinetic data will be collected using two floor-mounted force platforms (OR6-6, Advanced Mechanical Technologies Inc.) sampling at 2000 Hz. Kinematic data will be collected from 10 high-speed, high-resolution digital cameras (Raptor-E, Motion Analysis Corp.) that sample the movement of 22 reflective markers at 100 Hz. These reflective markers will be affixed to the participant’s skin according to a modified Helen Hayes marker set [40] bilaterally over the acromion processes, lateral epicondyles of the elbows, radial styloid processes, anterior superior iliac spines, lateral thighs, lateral femoral epicondyles, lateral tibiae, lateral malleoli, posterior calcanei, and on the ventral aspect of the feet over the bases of the 2nd metatarsal. A single marker will be placed over the sacrum. EMG data (Trigno^™^ Wireless EMG, Delsys Inc.) will collected at 2000 Hz by wireless surface electrodes placed bilaterally over the erector spinae, biceps femoris, quadriceps femoris, soleus and tibialis anterior muscles. The EMG data for each muscle group will be normalized to the maximum EMG recorded during three 5 s maximal voluntary isometric contractions performed while the participants are seated and secured onto the Biodex Isokinetic dynamometer (Model 900–860, Biodex Medical Systems, Inc.) using a methodology adapted from Hsu et al. [41]. The follow laboratory-based measures will be performed:*Self-selected walking speed:* Participants will complete five walking trials at a self-selected natural pace along a 10 m walkway. Whole body COM will be calculated throughout the trial based on the positions of the reflective markers and using published anthropometric calculations [42]. Average walking speed from each trial will be calculated over the middle 4 m of the walkway based on the calculated movement of the whole body COM separately for the paretic and non-paretic lower limb. The overall self-selected gait speed will be obtained by averaging across the five trials [43].*Physiological Balance Assessment:* Participants will be fitted into a safety harness attached to the ceiling and will stand (without assistive devices) with each foot on a separate force platform during the performance of the balance assessment tasks described below. Foot position on the platform will be standardized between outcome testing sessions using the tracings of each foot on paper adhered to the platforms. Participants will perform the following assessments:*Quiet stance:* Participants will be instructed to look at a visual target and “stand as still as you can”. Five 10 s trials will be recorded to determine resting baseline EMG activation levels for each muscle.*Limits of stability:* Participants will be asked to perform two maximal forward leans without raising their heels, hold the forward lean position for 5 s, and then return to their start position [44].*External perturbations:* A Postural Stress Test adapted from Wolfson et al. [45] will be performed. Participants will stand with their eyes open focusing on a visual target at eye level while a series of forward perturbation forces (1, 2, 3, 4, and 5% of body weight) are exerted via a horizontal cable attached to the participant’s hips using a pulley system hidden behind a curtain. Using this paradigm, it will be difficult for participants to anticipate the timing of the perturbations. Participants will be instructed to “remain standing in place on the platforms.” The onset of the load drop will be measured using an accelerometer attached to the load being dropped. The highest load tolerated without taking a step will be repeated 5 times [46].*Internal Perturbations:* Participants will be instructed: “When you are ready, raise your arm as fast as you can to shoulder height and hold it there” as they focus on a visual target at eye level [11]. Participants will perform 2–3 practice trials to familiarize themselves with the task and to receive any necessary correction on their performance. Ten trials with rest periods of 3–5 s between trials will be recorded. Arm acceleration magnitude will be measured using an accelerometer secured on the non-paretic hand to quantify the magnitude of the perturbation.*Stepping reactions:* To evaluate change in stepping performance, participants will be asked to perform 5 blocked trials with each leg as the lead stepping leg in the forward direction [15,47].

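### The held maximal forward lean is scored by peak COM-to-CP distance, from which lean distance cannot be recovered

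*Protocol article*

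**What the plan says.** Under Data collection methods, the limits-of-stability task asks participants to "perform two maximal forward leans without raising their heels, hold the forward lean position for 5 s, and then return to their start position". No instruction on lean speed is given.

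Under Analysis of mechanistic outcomes, the measure is the "resultant distance between the COM and CP in the transverse plane (COM-CP displacement"), computed at every data sample. The summary rule follows: "We will identify the maximum COM-CP displacement during each trial for physiological balance activities 2" b to e. Quiet stance has its own rule: "These parameters will also be used to quantify postural sway in quiet stance", labelled activity 2a. Limits of stability comes directly after quiet stance in the task list, so it is 2b and falls under the maximum rule.

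The same section gives the outcomes of all the physiological balance tests as EMG characteristics and "displacement of the whole body COM with respect to the centre of pressure (CP) including postural sway". It names no displacement of the COM or CP relative to the feet or the starting position.

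The later section, Analyses of mechanistic outcomes, compares COM-CP displacement between groups by ANCOVA. It leaves alpha unadjusted and relies on consistency across outcomes.

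**The concern.** A maximal lean with a hold is a test of how far forward a person can carry the body and keep it there. The stated score is the horizontal gap between COM and CP, and that gap does not measure reach. When the body is still, the vertical ground reaction must act under the COM or the body would topple, so the gap closes at every lean distance. The 5 s hold, which defines the task, contributes almost nothing to the score.

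The maximum then comes from the movement into or out of the lean or, if the lean is slow, from small corrections during the hold. FAST trains fast movement, while the control programme excludes fast stepping and high-velocity exercise. If FAST participants came to lean faster, they could score differently with no change in the distance they can hold.

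The favourable direction is also unclear. The mechanistic hypotheses expect reduced postural sway, whereas a longer or faster lean raises this score.

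**Working it through.** The article gives no figure for this point, so there is none to reproduce. The check has two parts.

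**1. The hold (no assumed values needed).** With feet in place and the body at rest, COM acceleration is zero and CP lies under COM. The distance is 0 cm for any lean distance.

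**2. The movement phases (illustrative values).** The Background refers to the inverted pendulum for standing balance: "Modest perturbations to quiet stance can be accommodated using an inverted pendulum model of balance control". Extending that model to the lean is my assumption. Treating the body as a point mass,

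|COM − CP| = (h / g) × |COM acceleration|, with g = 9.81 m/s².

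For a smooth (minimum-jerk) lean of distance D over time T, peak acceleration is 5.77 × D / T². Hence

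peak |COM − CP| = 5.77 × (h / g) × D / T².

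The documents give no COM height, lean distance or lean time. Assumed ranges: h from 0.85 to 1.05 m, D from 4 to 10 cm, T from 1 to 4 s, and a return that takes as long as the lean.

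At h = 0.95 m, the multiplier is 5.77 × 0.95 / 9.81 = 0.559 (T in s, D and score in cm):

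| D | T | Score |
|---|---|---|
| 8 cm | 1 s | 4.47 cm |
| 8 cm | 2 s | 1.12 cm |
| 8 cm | 4 s | 0.28 cm |
| 4 cm | 1 s | 2.24 cm |
| 10 cm | 2 s | 1.40 cm |

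- **Same reach, different time.** The 8 cm lean varies 4-fold between 1 s and 2 s, and 16-fold between 1 s and 4 s.
- **Ranking.** The 4 cm lean in 1 s outscores the 10 cm lean in 2 s, so the order by reach can reverse.
- **Sensitivity to height.** For h from 0.85 to 1.05 m, the 8 cm lean scores 4.00 to 4.94 cm (1 s), 1.00 to 1.24 cm (2 s) and 0.25 to 0.31 cm (4 s). Height matters little beside lean time.
- **Residual sway.** Assumed accelerations of 0.02 to 0.1 m/s² during the hold give (0.95 / 9.81) × acceleration = 0.19 to 0.97 cm. That range includes values above the 0.28 cm of the 4 s lean, so for slow leans the maximum may simply be sway.

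If the task were scored as forward displacement during the hold, these cases would score D itself (8, 4 and 10 cm) whatever the lean time.

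**The case against.** The strongest case on the other side has five parts.

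- **The stability limit is not a stated aim.** The mechanistic hypotheses cover walking speed, sway, EMG and balance confidence. The balance-test rows of Table 2 are the postural stress test, the arm raise and stepping reactions. The lean may be an ancillary task caught by a general rule. This stands and lowers the weight of the point. It does not remove it, because the rule names b to e and so covers the lean.
- **A condensed article may leave task-specific scoring elsewhere.** This stands in part: the accurate statement is that the article names no excursion score, not that none exists. But the point does not rest on silence. It rests on a stated rule applied to a task that it does not fit.
- **The score does contain distance.** This stands. At a fixed lean time it rises in proportion to D. A reader might infer that the score measures how fast people lean and not how far. That is too strong: it mixes the two as D / T², and distance cannot be separated out.
- **The arm difference is conjecture.** This stands. A reader might infer that the score is biased in favour of FAST. The article gives no lean times and no evidence that they will differ by arm, so it supports only the possibility.
- **The effect on conclusions is small.** This stands. The lean is one of several tasks and measures read together for consistency, and neither the follow-up nor the retention CB&M analysis uses it.

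**Conclusion.** The point holds in limited form. The maximum COM-CP rule does not suit activity 2b: the score is close to zero during the hold at any reach, and its trial maximum reflects acceleration or residual sway. Lean distance cannot be recovered from it. That conclusion rests on static equilibrium and on the article's own definition of the measure.

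The sizes (a 4-fold change when lean time halves, and possible reversal of ranking) rest on the pendulum model, a smooth lean, and assumed heights, distances and times. They show what can happen and do not estimate what will happen in this trial. A difference between arms produced by faster leaning alone is plausible, not shown.

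The reach is one exploratory mechanistic outcome. The criticism does not extend to quiet stance, the perturbation tasks or stepping reactions, and it leaves the CB&M results untouched. The change is still worth making because it is nearly free and would make the lean result interpretable.

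**What to change.** Take activity 2b out of the maximum COM-CP rule. Score it as forward displacement of the COM (or CP) during the 5 s hold, relative to the same participant's quiet-stance position. Normalising to foot length, from the tracings already made to standardise foot position, is one option. State how the two leans are combined and that a larger value is favourable. Fix the definition before unblinded data are examined. Leave the COM-CP rule as written for 2a and for 2c to 2e, so that stepping reactions keep their score.

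COM and CP coordinates are already to be calculated for each sample, and quiet stance is already recorded. The cost is one definition and one processing step, with no new data collection.

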### Sample size

Data from our published study of a similar FAST training protocol in individuals with chronic stroke showed an effect size of 1.9 SD with the intervention group and a pooled standard deviation of 7.45 for the pre and post CB&M score (primary outcome measure) [18]. Using our pilot data and a sample size equation suitable for our planned between-group comparisons using an analysis of covariance (ANCOVA); where we estimated that the magnitude of the association between the pre- and the post-intervention CB&M scores would be at least 0.75 and that a conservative estimate of effect size would be 0.60, we estimate that 30 participants per group (60 participants in total) are required to maintain a Type I error rate of 5% and 80% power to detect a difference between intervention groups. Therefore, recruitment will continue until a total of 30 participants in each group have completed the follow up assessment.

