Current clinical practice guidelines advocate task-oriented exercise programs involving the practice of ‘real life tasks’ following stroke [16], but specificity of task practice with respect to the speed required for postural reactions has received relatively little attention. A single session of fast functional squat and stepping training in stroke survivors has been found to improve paretic muscle activation and postural responses during an internal perturbation balance task after the exercises [15,17]. A recent case series reported improvements in walking balance that were retained for one year following a 12-session stepping retraining program in community-dwelling individuals with chronic stroke [18]. These changes in balance were accompanied by an increase in participation in meaningful activities in the community, and improvements in the movement kinematics of stepping reactions. These findings suggest that Fast muscle Activation and Stepping Training (FAST) may be an effective approach to improve walking balance following stroke.

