The primary objective of this assessor-blinded, parallel design, randomized controlled trial is to investigate the effectiveness of an outpatient FAST program commenced within the first six months following stroke compared to an active control intervention of conventional outpatient physiotherapy (active control) that includes no targeted fast movement training for improving walking balance. As many people fall in the first few months after discharge from inpatient rehabilitation, this was thought to be an important window for this balance intervention [19]. The primary hypothesis is that improvements in walking balance (as measured with the Community Balance and Mobility Scale, CB&M [20,21]) will be larger following 12 sessions of FAST intervention compared to 12 sessions of active control intervention. The secondary hypothesis is that CB&M scores will continue to be higher in the FAST group compared to the active control group one month following the intervention. Another aim of this study is to explore potential mechanisms associated with improvements in walking balance including; improvements in walking speed, balance self-efficacy, ability to respond to internal and external perturbations to balance and associated changes in postural muscle activation. Our *mechanistic hypotheses* are that compared to the active control intervention; the FAST retraining will result in:Increased fast and self-selected natural walking speed (gait assessment);Reduced postural sway (balance perturbation assessment);Improved timing and amplitude of muscle activation (EMG onset timing, burst area and slope) during balance perturbations and gait;Increased balance self-efficacy (using Activities-specific Balance Confidence (ABC) scale).

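### The between-group effect of 0.60 is called conservative but rests only on an uncontrolled pre-post change in chronic stroke, and the stated 80% power does not match its own inputs

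*Protocol article*

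**What the plan says.** The Sample size section of the protocol article gives one empirical source for the effect size, the team's earlier published work on a comparable program in chronic stroke. By the article's account, that work "showed an effect size of 1.9 SD with the intervention group and a pooled standard deviation of 7.45 for the pre and post CB&M score". The Background describes the same reference in these terms: "A recent case series reported improvements in walking balance that were retained for one year".

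For the planned ANCOVA between groups, the effect adopted is introduced with the words "a conservative estimate of effect size would be 0.60". On the covariate, the section assumes a "magnitude of the association between the pre- and the post-intervention CB&M scores would be at least 0.75". From these inputs it arrives at 30 participants per group for 80% power at a 5% Type I error rate. Recruitment continues until 30 in each group have completed the follow-up assessment, so 30 is a count of completers.

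The primary objective in the Background concerns a FAST program "commenced within the first six months following stroke compared to an active control intervention of conventional outpatient physiotherapy". Under Statistical analyses, the primary analysis is an ANCOVA of follow-up CB&M on treatment group with baseline CB&M as covariate.

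**The concern.** There are two linked problems in one paragraph.

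First, a pre-post change in treated patients and a difference between two randomised groups are different quantities. The second equals the first minus the change in the control group, and the paragraph has no figure for the control group. Controls in this trial receive the same number and length of individual sessions as the FAST group, including practice of standing balance and walking, so some improvement in them has to be expected. That 0.60 is smaller than 1.9 therefore does not make it conservative.

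Second, the stated combination of effect size, correlation, error rate and power does not lead to 30 per group.

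A reader of the eventual results will use this paragraph to judge what the trial could detect. As written, it claims empirical backing for the effect size that it does not have, and it misstates the sensitivity of the chosen sample.

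**Working it through.** **Inputs (protocol article, Sample size and Primary analysis).** Between-group effect d = 0.60; pre-post correlation r = 0.75 (the floor of the stated range); Type I error 5%; power 80%; equal groups; n = 30 completers per group; ANCOVA with one covariate. Sidedness is not stated. Two-sided is taken as the main case.

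**1. Try to reproduce 30 per group.**

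ANCOVA reduces the residual variance by the factor 1 − r² = 1 − 0.5625 = 0.4375. By the normal approximation:

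n per group = 2 × (1 − r²) × (z₀.₉₇₅ + z₀.₈₀)² / d² = 2 × 0.4375 × (1.960 + 0.842)² / 0.36 = 19.1, so 20.

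The noncentral t distribution gives 79.8% power at 20 per group and 81.8% at 21, hence about 20 to 21.

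Other readings at 80% power also fail to give 30:

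| Reading | Two-sided n per group | One-sided n per group |
|---|---|---|
| ANCOVA, r = 0.75 | 20 | 16 |
| No covariate | 44 | 35 |
| 0.75 read as r² | 11 | 9 |
| Change score, variance factor 2(1 − r) | 22 | 18 |

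An allowance for loss does not explain the figure, because 30 is defined as the number who complete follow-up. A correlation of about 0.56 would give 30, but the text says at least 0.75.

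**2. Power actually delivered by 30 per group.**

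Noncentrality = d / √(1 − r²) × √(n/2) = 0.60 / 0.6614 × √15 = 3.51, with 2n − 3 = 57 degrees of freedom and a two-sided critical value of 2.002. Power is 93% (94% by the normal approximation). A one-sided test gives 97%.

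**3. Effect at which 30 per group has 80% power.**

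Solving the same expression for 80% power with r = 0.75 gives d = 0.487, or about 0.49. In CB&M points this is 0.487 × 7.45 = 3.6, if the SD of 7.45 applies here. The normal approximation gives 0.48.

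**4. What supports 0.60.**

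| | Source cited for sizing | This trial |
|---|---|---|
| Design | Case series | Randomised, two groups |
| Quantity | Pre-post change in treated patients, 1.9 SD | FAST minus active control at follow-up, 0.60 |
| Population | Chronic stroke | Within six months of stroke |
| Change in controls | None available | Not stated |

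The step from 1.9 to 0.60 is not derived from any control-group figure.

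**5. Sensitivity, as labelled assumptions only.** Power at 30 per group, two-sided 5%, by the method of step 2. The article gives no source for effects below 0.60, and r = 0.50 lies below its stated floor.

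| Assumed effect (SD) | r = 0.75 | r = 0.50 |
|---|---|---|
| 0.60 | 93% | 75% |
| 0.50 | 82% | 59% |
| 0.40 | 63% | 42% |
| 0.30 | 41% | 26% |

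**The case against.** The best defence is that the paragraph is largely open about its source. It names chronic stroke, attributes 1.9 SD to the intervention group, and ties the SD to pre and post scores. It does not plan on 1.9 but on about a third of it (0.60 / 1.9 = 0.32). The sample is also larger than the stated inputs need, so planned power is kept down to about 0.49 SD if r = 0.75 holds. All of this stands, and it limits the consequence. It does not make 0.60 a conservative estimate, because the comparison with 1.9 is between unlike quantities.

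A reader might go further and infer that 0.60 is too large and the trial underpowered. One could argue that if FAST again gained 1.9 SD (1.9 × 7.45 = 14.2 points), a difference of 0.60 requires controls to gain no more than 1.3 SD (9.7 points, 68% of the FAST gain), and that active physiotherapy early after stroke may achieve more. The documents do not support that conclusion. They give no control gain. The argument carries a chronic-stroke gain into a subacute population while raising only the control side, although natural recovery occurs in both randomised arms and cancels in the difference if it is additive. It also assumes that 0.60 and 1.9 share the same SD, which the article does not say. Even on these terms, a control gain of 75% of the FAST gain (d = 0.25 × 1.9 = 0.475) would leave power at 78%.

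Nor do the documents support a claim that the SD will be well above 7.45. No larger value is given, the target is stated in SD units, and a wider case mix might also raise the correlation, for which 0.75 is only the floor.

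**Conclusion.** The point holds in two parts. First, 0.60 is an assumption with no controlled or subacute evidence behind it in the article, and calling it conservative is not justified. It is unsupported, not disproved. Second, the power statement is numerically wrong on its own inputs: 30 per group gives about 93% power at 0.60, not 80%; about 20 to 21 per group would give 80%; and 30 per group has 80% power at about 0.49 SD.

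These figures assume a two-sided 5% test, r = 0.75, ANCOVA with one covariate, and 30 completers per group. The conversion to 3.6 points also assumes that the chronic-stroke SD of 7.45 carries over. The numerical error runs in the safe direction: the sample is larger than the stated inputs need. The matter is therefore one of correct justification and reporting, and gives no ground to change the design.

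**What to change.** In the Sample size section:

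- State that 1.9 SD is an uncontrolled within-group change in chronic stroke, and that 0.60 is an assumed between-group effect not derived from controlled data. Remove the word conservative.
- Replace the power sentence with what the design delivers: 30 completers per group give about 93% power at 0.60 SD and 80% power at about 0.49 SD (3.6 CB&M points if the SD is 7.45), for r = 0.75 and a two-sided 5% test. State the sidedness.
- If power for smaller differences or a lower correlation is shown, label those values as assumptions.

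Two additions are better left out. Scenarios with a larger SD have no source in the article. A rule that judges a null result by whether the confidence interval excludes 4.5 points (0.60 × 7.45) would rest on the same unsupported figures.

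The cost is a few sentences. Enrolment, procedures and the primary analysis stay as they are.

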#### Primary analysis

We will perform an analysis of covariance (ANCOVA), where the baseline CB&M score serves as the covariate; treatment group as the independent variable, and the follow up CB&M score as the dependent variable. To test our secondary hypothesis about retention, we will repeat this analysis with the retention CB&M score as the dependent variable.

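### The stated requirement of 30 per group for 80% power does not follow from the ANCOVA inputs given with it: on the natural reading about 21 per group suffice and 30 give about 93%

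*Protocol article*

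**What the plan says.** The Sample size section of the protocol article bases the calculation on an equation suited to ANCOVA, without showing the equation. It takes 0.60 for the effect size, a value it calls conservative. For the correlation it assumes that "the magnitude of the association between the pre- and the post-intervention CB&M scores would be at least 0.75". It concludes that "30 participants per group (60 participants in total) are required to maintain a Type I error rate of 5% and 80% power". A pooled SD of 7.45 for the Community Balance and Mobility Scale (CB&M) is quoted from an earlier study in chronic stroke, but the text does not say whether 0.60 is expressed in that SD. Sidedness is not stated either.

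The section then derives a recruitment rule from the figure: enrolment goes on until each group has 30 participants with a completed follow-up assessment. The 30 are therefore completers.

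The Primary analysis section confirms the model: follow-up CB&M is the dependent variable, "where the baseline CB&M score serves as the covariate; treatment group as the independent variable".

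**The concern.** The section gives a closed set of inputs (model, effect size, correlation, Type I error, power) and a result, so the result can be checked. A correlation of 0.75 between baseline and follow-up removes more than half of the outcome variance in an ANCOVA. An effect of 0.60 SD should then need far fewer than 30 per group for 80% power.

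This is the article's only power statement, and the recruitment target rests on it. A reader is told that 30 per group is the minimum for an effect of 0.60. If that is wrong, the reader cannot tell what margin the trial has against a smaller effect or a weaker correlation. The margin matters because the planning data come from chronic stroke, while the trial enrols people within six months of stroke. The unstated SD scale also decides whether the trial has power to spare or too little.

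**Working it through.** **Inputs from the Sample size section.** Type I error 5%; power 80%; effect size d = 0.60; correlation r = 0.75 (stated as a minimum); 30 per group, all completers; equal groups. **Assumptions for the main calculation, because the text is silent:** two-sided test; d in units of the raw outcome SD.

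**1. ANCOVA requirement, normal approximation.**

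n per group = 2(z₀.₉₇₅ + z₀.₈₀)²(1 − r²)/d²

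- Variance factor: 1 − 0.75² = 1 − 0.5625 = 0.4375.
- Unadjusted size: 2(1.960 + 0.842)²/0.60² = 15.70/0.36 = 43.6.
- With the covariate: 43.6 × 0.4375 = 19.1, so 20 per group.

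**2. t-based check.** This uses a noncentral t with 2n − 3 degrees of freedom and allows for chance baseline imbalance. A simulation of the ANCOVA with 20,000 runs per row is set beside it.

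| n per group | Noncentral t | Simulation |
|---|---|---|
| 20 | 78.7% | 79.1% |
| 21 | 80.8% | 80.2% |
| 30 | 92.8% | 93.2% |

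The t-based requirement is 21 per group. At 30 per group the normal approximation gives 94.0%, so about 93% is a fair summary.

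**3. Can the stated 30 be reproduced from the stated inputs?** Requirement per group at 80% power:

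| Reading | Normal | t-based |
|---|---|---|
| ANCOVA, two-sided, raw SD | 20 | 21 |
| ANCOVA, one-sided, raw SD | 16 | 17 |
| Change score, two-sided | 22 | 23 |
| 0.75 taken as R², two-sided | 11 | 13 |
| No covariate gain, two-sided (same as 0.60 in covariate-adjusted SD units) | 44 | 45 |
| No covariate gain, one-sided | 35 | 36 |

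None gives 30. A correlation above 0.75 lowers the requirement further, so the words *at least* do not help. Getting from 20 to 30 by dropout inflation would take about 33% loss (20/0.67 = 29.9), but the 30 are already completers.

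**4. Effect of the SD scale.** If 0.60 is already in covariate-adjusted SD units, r no longer enters and 44 to 45 per group are needed. Power at 30 per group is then 62.0% by noncentral t with the covariate and the imbalance allowance, and 62.7% without them. The normal approximation gives 64.2%.

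**5. What 30 completers per group buy on the raw-SD reading.** Solving the noncentral t calculation of step 2 for 80% power at n = 30:

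- r held at 0.75: d = 0.49. If 7.45 is the relevant SD (an assumption), that is 0.49 × 7.45 = 3.7 CB&M points, against 0.60 × 7.45 = 4.5 points.
- d held at 0.60: r = 0.59.

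The normal formula gives slightly more favourable limits, d = 0.48 and r = 0.56.

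**The case against.** The strongest reply is that the article does not show its equation, the sidedness or the SD scale, so nobody can assert a replacement power without condition. That stands. The 93% depends on the two-sided, raw-SD reading. That reading is the natural one, because a correlation of 0.75 has no part in the equation if 0.60 is already covariate-adjusted, but the text does not settle it. What needs no such choice is that none of the readings gives 30.

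A second reply is that no harm follows. On the natural reading the trial has more power than it claims, and the primary ANCOVA and the Type I error rate are untouched. That also stands, and it limits the severity.

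Three stronger inferences are tempting, and the documents do not support them:

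- **A particular slip explains the 30.** Applying √0.4375 = 0.661 where 0.4375 belongs gives 45 × 0.661 = 29.8 (28.8 from the unrounded 43.6). Entering 0.5625 as if it were r gives 43.6 × (1 − 0.5625²) = 29.8. A change-score test at 90% power also gives 30 by the normal formula. Several routes reach the figure and the text points to none of them.
- **The extra participants are an attrition allowance.** The section counts 30 per group at completed follow-up, so losses are met by continued recruitment and not by padding within the 30.
- **The trial is underpowered.** That follows only if 0.60 is on the covariate-adjusted scale, which the article does not say.

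**Conclusion.** The concern holds: the sample size sentence is wrong as written, because its stated inputs do not lead to 30 per group at 80% power. With a two-sided 5% test and 0.60 in raw-SD units, about 20 to 21 per group suffice and 30 completers per group give about 93%. With 0.60 in covariate-adjusted SD units, 44 to 45 are needed and 30 give about 62 to 63%. The two readings err in opposite directions, so the scale has to be stated.

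This is an error of reporting and justification, conservative on the natural reading. It does not undermine the primary analysis and gives no reason to change the size of the trial on that reading. It should be fixed, but it is not critical. The conclusion rests on the printed values of 0.60, 0.75, 5% and 80%, on equal groups, and on the usual ANCOVA variance factor 1 − r².

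**What to change.** State the sample size equation, the sidedness of the test and the SD to which 0.60 refers, and correct the sentence to match. On the two-sided, raw-SD reading it could run:

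*About 21 per group suffice for 80% power at effect size 0.60 and r = 0.75; 30 completers per group give about 93%, and keep 80% power for an effect of about 0.49 or a correlation of about 0.59.*

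Keep the existing rule of recruiting to 30 completers per group. Present the excess over 21 as a margin for a smaller effect or a lower correlation, not as an attrition allowance.

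On the raw-SD reading this costs a sentence or two and no extra participants. If the sponsor finds that 0.60 was meant on the covariate-adjusted scale, the stated power must come down to about 62 to 63%, or the assumptions and the target must be revisited.
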